### Primary and secondary outcomes

The primary outcomes include:

Duration of mechanical ventilation to successful extubation defined as the time from the start of mechanical ventilation, defined as either the time of intubation in the ICU, or the time of admission to the ICU following previous intubation for surgery, and until successful extubation, with successful extubation defined as ≥48 hours of unassisted spontaneous breathing after extubation.

Unassisted spontaneous breathing is defined here to include supplementary oxygen and support with high-flow nasal catheters. Patients with non-invasive mask ventilation are considered to be assisted.

The secondary objectives of the trial are to compare the following variables in the standard care group and BEACON Caresystem group:

Duration of mechanical ventilation to successful extubation following randomisation defined as the time from randomisation and until successful extubation, with successful extubation defined as ≥48 hours of unassisted spontaneous breathing after extubation.Time from control mode to support mode defined as the time following randomisation, from initiation of control modes of ventilation and until initiation of support modes of ventilation.Time from support mode to successful extubation defined as the time following randomisation, from initiation of support modes of ventilation and until successful extubation.Number of changes in ventilator settings per day defined as the daily registered number of changes to ventilator settings from randomisation until successful extubation.Time to first SBT defined as the time from randomisation to the first performed SBT.Time to first successful SBT defined as the time from randomisation to the first successful SBT.Time to first extubation defined as the time from randomisation to the first extubation attempt.Time to first disconnection from mechanical ventilation defined as the time from randomisation to the point at which mechanical ventilation is first discontinued.Percentage of time in control mode ventilation defined as the time from randomisation which is spent in controlled modes of mechanical ventilation in per cent of duration of mechanical ventilation.Percentage of time in support mode ventilation defined as the time from randomisation which is spent in support modes of mechanical ventilation in per cent of duration of mechanical ventilation.Use of sedatives defined as the cumulative use of sedative drugs from randomisation until successful extubation.Use of neuromuscular blockading agents defined as the cumulative use of neuromuscular blockading agents from randomisation until successful extubation.Number of intubation free days defined as the number of days without intubation from randomisation until successful extubation.Number of reintubations defined as the number of reintubations following extubation from randomisation until successful extubation.Number of tracheostomies defined as the number of patients having tracheostomy performed from randomisation until successful extubation or protocol end.Number of patients on prolonged mechanical ventilation defined as the number of patients on mechanical ventilation ongoing for more than 21 days after the start of mechanical ventilation.Number and types of adverse events related to mechanical ventilation defined as the incidence of adverse events directly related to mechanical ventilation.ICU mortality defined as the mortality from randomisation and until death or ICU discharge.Length of stay defined as the duration of ICU admission from the start of mechanical ventilation and until death or ICU discharge.Mobilisation times defined as the time from randomisation until (1) first mobilisation, for example, sitting on the edge of the bed, standing up and marching on the spot and (2) regaining independency, for example, able to drink/eat or comb hair.Daily patient physiological blood gas status defined as daily ABG values of SaO_2_, PaO_2_, PaCO_2_, pH from randomisation until successful extubation.Daily average physiological status defined as daily averages of measured values of oxygenation (SpO_2_), end-tidal CO_2_ fraction (EtCO_2_), ventilation (respiratory rate, tidal volume, anatomical dead space), pulmonary mechanics (airway pressure, respiratory system compliance) and ventilator settings as measured routinely at the bedside.

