### Eligibility criteria

#### Inclusion criteria

At least 24 hours of invasive mechanical ventilation.Age ≥18 years.Patient is mechanically ventilated in a ventilator mode, and by a ventilator, supported by the BEACON Caresystem.Haemodynamically stable, where instability is defined by the presence of two or more of the following criteria: acidosis pH <7.2, poor urine output <0.5 mL/kg/h, use of vasopressors, for example, noradrenaline >25 µg/min.

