#### Exclusion criteria

The absence of an arterial catheter for blood sampling.Medical history of home mechanical ventilation which may lead to prolonged stay in the ICU, including long-term oxygen therapy and non-invasive ventilation not associated with sleep apnoea.Clinical conditions requiring treatment with extracorporeal membrane oxygenation (ECMO), that is, an inspired oxygen of 100% for more than 24 hours.Head trauma or other conditions where intracranial pressure may be elevated and tight regulation of arterial CO_2_ level is paramount.Primary (non-overdose related) neurological patients (Glasgow Coma Score 24).Severe heart failure classified by grade 4 American Heart Association guidelines.End-stage liver disease.Multiple ICU admissions within the medical stratification group, that is, more than one admission.Corrective orthognathic surgery.ICU admission following oesophageal surgery.Patients with morbid obesity defined as either body mass index (BMI)≥45; or BMI≥35 with an Acute Physiology and Chronic Health Evaluation II (APACHEII) score on admission >24.Pregnancy.Mechanical ventilation initiated for more than 24 hours in other centres.

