### Randomisation

Figure 1 illustrates the CONSORT flow diagram for the study. On recruitment to the trial, participants are randomised to either to the intervention group where advice is provided by the BEACON Caresystem, or to the control arm where standard care is provided. Block randomisation is applied with each block stratified to ensure equal distribution between control and intervention arm for the following patient groups, reducing the risk of potential bias by over-representation of these groups in the control or intervention arms:

Surgical or medical ICU admission.Presence of absence of chronic obstructive pulmonary disease.Primary thoracic or non-thoracic medical diagnosis.

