
### Statistical considerations

Sample size was determined by a power analysis of duration of mechanical ventilation. Extrapolation of the 2016 ICU admission data from two London-based NHS hospitals provided a sample size of 548 patients over an 18-month period. In these patients, mean total duration of mechanical ventilation measured in days was 7.2, with an SD of 7.0 days. A study population of 137 patients in each randomisation group would allow detection of a 2 day or 30% improvement in the duration of mechanical ventilation in the BEACON Caresystem group assuming a similar improvement in SD, with an α level of 0.05 and power of 0.8. A 2 days or 30% reduction in duration of mechanical ventilation is similar to that used previously.^6^

Primary and secondary outcomes will be measured across the protocol duration and comparison made by independent samples t-test, or appropriate non-parametric testing if not normally distributed. Complementary analysis will be performed using Kaplan-Meier curves.

The study is not sufficiently powered to allow subgroup analysis for the groups specified in the randomisation strategy.

An independent data safety monitoring committee will be established as part of the study, with this committee responsible for defining stopping criteria. Safety data will be looked at after the first 80 patients have been recruited, with an interim analysis performed following 50% recruitment.

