## Discussion

This paper presents the study protocol of single-blinded multicentre randomised control trial evaluating management of mechanical ventilation as directed by the BEACON Caresystem compared with that of standard care in the general intensive care setting. To test the hypothesis that following advice from the BEACON Caresystem will reduce time to successful extubation, patients are randomised to care including advice from the system, or standard care. In addition, as secondary outcomes, the study will investigate whether application of the advice changes the time spent in control ventilation modes, the number of changes made to the ventilator, the use of medication such as sedative or neuromuscular blocking agents, the changes in clinical procedures such as reintubation or tracheostomy and clinical and physiological status of the patient. Although not powered to detect differences between groups, it will also investigate the length of stay at the ICU and patient mortality.

This study is the next step in evaluation of the advice of the BEACON Caresystem. A large number of studies have been performed validating the physiological models included in the system, as summarised in,^9^ and studies of short duration have been performed evaluating the physiological response to application of advice.^14 15^ This use of the system over the whole duration of ICU stay allows for assessment of more meaningful clinical outcomes, relating to the time spent on mechanical ventilation. In addition, the study includes only patients intubated for a minimum of 24 hours, meaning that short-term postoperative patients who may have rather uncomplicated intubation periods are not included.

The study includes limitations. The study was powered on duration of mechanical ventilation rather than duration to successful ventilation, this being the historical data available during study design. The study is not powered to detect changes in mortality, and does not follow-up on the patients after transfer from the ICU. In the context of this study, successful extubation is defined as the lack of need for non-invasive ventilator support for 48 hours after extubation, rather than successful rehabilitation of the patient subsequent to their ICU stay.

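### The primary duration counts ventilation before randomisation, which adds noise the device cannot affect, and its start rule gives no time zero for some eligible patients

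*Protocol article*

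**What the plan says.** Under Primary and secondary outcomes, the primary duration runs to successful extubation from a start "defined as either the time of intubation in the ICU, or the time of admission to the ICU following previous intubation for surgery". No other case is listed.

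The Inclusion criteria require "At least 24 hours of invasive mechanical ventilation", and the Discussion repeats that "the study includes only patients intubated for a minimum of 24 hours". Under Randomisation, "On recruitment to the trial, participants are randomised", so allocation follows once the 24 hours are met. The only limit on earlier ventilation is in the Exclusion criteria: "Mechanical ventilation initiated for more than 24 hours in other centres". None is set for the trial's own ICUs. One stratification factor is "Surgical or medical ICU admission", so non-surgical patients are expected.

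The first secondary outcome is the same endpoint on a different clock: "Duration of mechanical ventilation to successful extubation following randomisation defined as the time from randomisation and until successful extubation". Statistical considerations sizes the trial on historical totals, where "mean total duration of mechanical ventilation measured in days was 7.2, with an SD of 7.0 days". It plans 137 patients per arm for a 2 day or 30% reduction, with a t-test or a non-parametric test, complemented by Kaplan-Meier curves.

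**The concern.** Two separate problems sit in the one definition.

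First, the interval from clock start to randomisation is part of the primary outcome, and the device cannot change it. If it varies between patients, it adds variance without adding signal. The effect assumed for the sample size is a share of total time, but it has to be earned from the time after randomisation alone. In the Kaplan-Meier analysis, patients sit in the risk set during time in which no trial event could have been observed, because anyone extubated earlier would not have been enrolled.

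Second, the two start events do not cover everyone who can be enrolled. A medical patient intubated in an emergency department, on a ward or in another hospital fits neither. Sites could then time the primary outcome differently. The same start also anchors ICU length of stay and the count of patients ventilated for more than 21 days.

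**Working it through.** **Inputs from the document.** Control mean 7.2 days, SD 7.0; difference 2 days or 30% (0.30 × 7.2 = 2.16 days); SD improving similarly, read as 0.7 × 7.0 = 4.9; 137 per arm; α 0.05, taken as two-sided; power 0.80.

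**Inputs assumed.** The document gives neither the mean nor the spread of the time from clock start to randomisation (the lag, L). I use means of 1 to 3 days and SDs of 0 to 2 days. I also take 7.2 days as the control mean on the primary clock.

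**Step 1: the plan's own figure.** SE = √((7.0² + 4.9²)/137) = √(73.01/137) = 0.730. Power for 2.0 days = Φ(2.0/0.730 − 1.96) = 0.78; for 2.16 days it is 0.84. The stated 0.80 lies between them, so the planning figure is reproduced closely enough to work from.

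**Step 2: the cut needed after randomisation.** Required cut = difference/(7.2 − L).

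| Mean lag (assumed) | Mean time after randomisation | For 2.0 days | For 2.16 days |
|---|---|---|---|
| 1 day | 6.2 | 32% | 35% |
| 2 days | 5.2 | 38% | 42% |
| 3 days | 4.2 | 48% | 51% |

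**Step 3: what changing the clock recovers.** If L is constant, subtracting it leaves the difference in days, both SDs and all ranks unchanged, so power is the same on either clock. Only variation in L matters. With an independent lag of SD s and total control SD 7.0, the post-randomisation SD is p = √(49 − s²). With a 30% cut in post-randomisation time, the intervention-arm SD is 0.7p from randomisation and √((0.7p)² + s²) on the total clock.

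| Lag mean, SD | Difference (days) | Power, total clock | Power, from randomisation |
|---|---|---|---|
| 2, 1 | 0.3 × 5.2 = 1.56 | 0.57 | 0.58 |
| 2, 2 | 1.56 | 0.56 | 0.61 |
| 3, 2 | 0.3 × 4.2 = 1.26 | 0.40 | 0.44 |

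Simulated trials with a skewed lag (1 day plus an exponential of mean 1 or 2 days) give t-test gains of about 0 to 6 points. Rank-test gains are about 2 to 3 points if post-randomisation time is gamma. If it is lognormal, rank-test power rises from 76% to 82% for the shorter lag and from 50% to 73% for the longer. The rank test is relevant because a mean of 7.2 with an SD of 7.0 implies strong skew, and the plan provides for a non-parametric test in that event.

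**Step 4: adjusting is equivalent to moving the clock.** Total duration minus lag equals post-randomisation duration. A linear regression of total duration on arm and lag therefore gives the same treatment estimate as a regression of post-randomisation duration on arm and lag. The precision can be had without changing the primary outcome.

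**Step 5: coverage of the start rule.** Ventilation elsewhere for up to 24 hours is not excluded, and medical admissions are stratified for. Neither start event applies to a medical patient intubated outside the ICU. For a transfer from another centre, intubation and ICU admission could differ by up to 24 hours, against a planned difference of 2 days. This step needs no assumption about the lag.

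**The case against.** Total duration is a legitimate endpoint for patients, it matches the historical data used for sizing, and the planned effect is stated on that same scale. The from-randomisation version is already the first secondary outcome, so readers will see it. The interval precedes allocation and the Kaplan-Meier analysis is only complementary. Covariate adjustment is often left to an analysis plan, and the gain in power rests on lags that nobody has reported. All of this stands, and it limits the point to precision.

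Three stronger readings are tempting, and the document does not support them.

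- *Every patient carries at least 24 fixed hours in the primary outcome.* For patients intubated for surgery the clock starts at ICU admission, so theatre ventilation is not counted and their lag may be under 24 hours.
- *The clock drops power from 80% to about 72% or 57%.* Those figures arise from assuming that the true effect is 30% of post-randomisation time only (1.86 or 1.56 days at a constant lag of 1 or 2 days, SDs 7.0 and 4.9). That is a smaller effect than the plan assumes, and moving the clock does not recover the loss.
- *The comparison is biased.* The lag is fixed before randomisation and so is balanced in expectation.

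The objection does not answer the missing start time. The article's definition reads as exhaustive and omits patients whom its own criteria admit.

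**Conclusion.** The point holds as a matter of precision and definition. The primary outcome includes time that the device cannot influence, with no limit in the trial's own ICUs and a 24 hour limit only for other centres. The planned difference therefore requires a post-randomisation cut of 32-35% at a mean lag of 1 day or 38-42% at 2 days, against the stated 30%. Removing or adjusting for the lag adds roughly 0-6 points of t-test power and 2-23 points of rank-test power under assumed mean lags of 2-3 days with SD 1-2. The upper end depends on a lognormal shape and the longer lag, and a constant lag gives no gain. The missing time zero for patients intubated outside the ICU and not for surgery is the firmest part, since it follows from the text alone.

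**What to change.** 1. **Preferred: keep total duration as primary.** Adjust it for hours ventilated before randomisation, and use randomisation as the entry time in the Kaplan-Meier analysis. This changes analysis wording only.
2. **Alternative, only if no unblinded or interim data have been seen:** make the from-randomisation duration primary and total duration secondary. Both are already defined, so the cost is an amendment and a registry update. The result would compare less directly with the historical total-duration figure, and a late swap carries a credibility cost, particularly as an interim analysis is planned at 50% recruitment.
3. **In either case, state one start time for patients intubated outside the ICU and not for surgery.** It should be consistent with the existing surgical rule, for example admission to the trial ICU. Taking first intubation at any location for everyone would bring in the theatre time that the present rule leaves out and would lengthen the pre-randomisation interval. This is a one-sentence clarification, to be applied identically at all sites and in both arms.

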#### Mode/sedation

If the BEACON Caresystem detects substantial spontaneous breathing during control ventilator modes, advice is provided to consider changing to support mode. Additionally, if pH falls below a defined value in support mode, advice is provided to consider changing to control mode or modifying sedation. In either situation, the protocol dictates that the bedside nurse consults with the clinician on duty.

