#### Spontaneous breathing trial (SBT)

During weaning from mechanical ventilation, the BEACON Caresystem monitors the levels of Pressure Support (PS) and Positive End Expiratory Pressure (PEEP). When these levels are reduced to values below clinical guideline thresholds,^21^ the BEACON Caresystem automatically monitors variables evaluating spontaneous breathing criteria. If these remain within limits and for a duration determined by international guidelines,^21^ the system prompts the user to assess the appropriateness of extubation and provides a checklist to help. The primary function of the BEACON Caresystem with regards weaning is to reduce levels of support where possible; it does not suggest an active SBT or extubation. As such, the decision to extubate is according to standard clinical practice for both arms of the study, meaning that at any time the clinical team can perform an active SBT or extubate the patient without confirmation from the system. Reintubation is documented by the research team and the participant enters a standard care pathway, which involves the deactivation of the BEACON Caresystem. The participant is then followed up until the end of the protocol (figure 1).

The protocol ends with transfer or discharge from ICU or death (figure 1).

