To encourage use of the system and perform an evaluation where advice is applied, the application of advice is mandatory. As clinical practice is variable and advice is unlikely to be applied in all cases, the application and effects of advice are monitored by the BEACON Caresystem, and can be interrogated to ensure that the proposed changes have been made and that the effects are considered safe in cases of doubt.

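### The interval from support mode to successful extubation starts at an event the device influences, so testing it between arms is not a randomised comparison of weaning; the start of the control-to-support interval is also unclear

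*Protocol article*

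**What the plan says.** All references are to the protocol article.

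- **Primary and secondary outcomes** lists two mode-related intervals to be compared between arms. Control-to-support time is "the time following randomisation, from initiation of control modes of ventilation and until initiation of support modes of ventilation". Support-to-extubation time is "the time following randomisation, from initiation of support modes of ventilation and until successful extubation". The same list has several outcomes timed from randomisation, including successful extubation, first SBT and first extubation.
- **Mode/sedation** describes what the system does about mode: "If the BEACON Caresystem detects substantial spontaneous breathing during control ventilator modes, advice is provided to consider changing to support mode". It also works in the other direction: "if pH falls below a defined value in support mode, advice is provided to consider changing to control mode or modifying sedation". In both situations the nurse consults the clinician on duty.
- **Inappropriate suggestions for changes in ventilator settings** says that "the application of advice is mandatory". **Study procedure** has advice disabled in the control arm, with data still recorded by the device.
- **Spontaneous breathing trial (SBT)** says that "the decision to extubate is according to standard clinical practice for both arms of the study".
- **Inclusion criteria** require "At least 24 hours of invasive mechanical ventilation" and accept any ventilator mode that the system supports.
- **Statistical considerations** plans a t-test or a non-parametric alternative for primary and secondary outcomes, with Kaplan-Meier curves as a complement. No adjustment is mentioned.

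**The concern.** A between-arm test is protected by randomisation only if time zero, and membership of the groups compared, are fixed at or before randomisation. Support-to-extubation time meets neither condition. Its start is an event on which the device advises in one arm only, and a patient who never reaches support mode has no value.

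A device that succeeds in starting support earlier can therefore show a longer weaning interval for that reason alone. A formally tested secondary outcome could then appear to contradict the time to extubation, and the reader could not tell a slower wean from an earlier start.

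Control-to-support time has a different problem. Support mode is the end of that interval, so starting support earlier shortens it. What is unclear is the start: patients have been ventilated for at least 24 hours at entry, so control mode may already have begun, or have already given way to support mode.

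**Working it through.** **The plan's own figures.** The document gives no planning figure for either interval. Its only sample-size figure, 137 per arm, is for duration of ventilation and does not bear on the argument; it serves below only as the size of a simulated trial. It is roughly reproducible: a difference of 2 days, SDs of 7.0 and 4.9 (30% lower) averaged to 5.95, two-sided 0.05 (sidedness is not stated) and 80% power give 2 × (1.96 + 0.842)² × 5.95² / 2² ≈ 139 per arm.

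**Formula.** Let T_sup and T_ext be the times from randomisation to support mode and to successful extubation, and let W = T_ext − T_sup. If the device brings support forward by d days and extubation forward by e days:

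- change in T_ext, counted from randomisation = −e, whatever d is;
- change in W, counted from support mode = (T_ext − e) − (T_sup − d) − W = d − e.

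**Example.** The days are assumed, not taken from the document. Control arm: support on day 3, extubation on day 6, so W = 6 − 3 = 3 days. In the device arm support starts on day 2 (d = 1).

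| e (days) | Extubation, device | W, device | W, control | Device minus control |
|---|---|---|---|---|
| 0 | day 6 | 6 − 2 = 4 | 3 | +1.0 (33% longer) |
| 0.5 | day 5.5 | 5.5 − 2 = 3.5 | 3 | +0.5 (17% longer) |
| 1 | day 5 | 5 − 2 = 3 | 3 | 0 |
| 2 | day 4 | 4 − 2 = 2 | 3 | −1.0 (33% shorter) |

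In the second row the patient leaves the ventilator half a day sooner and the outcome reads half a day worse.

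**How often a test would show it.** This was an illustrative simulation with 137 per arm, 4,000 runs and a two-sided t-test at 0.05. It assumed exponential times in the control arm with means of 2 days (randomisation to support) and 4 days (support to extubation), and every patient reaching both milestones after randomisation. None of these assumptions is in the document.

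| d | e | Mean change in W | W significantly worse | W significantly better |
|---|---|---|---|---|
| 0.5 | 0 | +0.5 | 16% | 0.2% |
| 1 | 0 | +1.0 | 46% | 0% |
| 1.5 | 0 | +1.5 | 74% | 0% |
| 1 | 0.5 | +0.5 | 16% | 0.2% |
| 1 | 1 | 0 | 2% | 2% |
| 1 | 2 | −1.0 | 0% | 64% |

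**Control-to-support time.** Two readings of "the time following randomisation, from initiation of control modes of ventilation and until initiation of support modes of ventilation" fit the text. The clock may start at randomisation for a patient already in control mode, or only control episodes begun after randomisation may count. The two readings give different patients and different values. Neither says what to do with a patient already in support mode at entry. Because modes can alternate, the definition also leaves open which episode counts.

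**The case against.** **The device does not dictate the mode.** The advice is to consider a change, and the clinician is consulted. That is true, but influence in one arm only is enough for the start of the clock to differ between arms.

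**The interval need not lengthen.** This stands. A reader might infer that earlier support mode always makes the device look worse. It does so only when e < d. The trial is planned around a 2-day gain; if all of that were gained after randomisation with support 1 day earlier, the interval would favour the device. Because extubation is left to usual practice in both arms, e < d is possible, but the document does not show it to be likely.

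**The same penalty does not apply to both intervals.** This also stands. For control-to-support time, earlier support favours the device.

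**Selection and mode at entry are unknown.** A reader might infer that patients moved earlier to support are sicker, or that most patients have no valid start for control-to-support time. The document supports neither. The advice is triggered by spontaneous breathing, no mode distribution at entry is given, and the words about time following randomisation can reasonably be read as starting the clock there. This part is an ambiguity that the full protocol or SAP may settle.

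**Sound comparators are already listed.** They are, and they limit the damage: a reader who sees the randomisation-based outcomes alongside could work out that the start had shifted. They do not make the test of W itself valid.

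**Conclusion.** The point holds as a minor one. As defined, support-to-extubation time is a contrast between groups formed after randomisation, with a start that the intervention can move, and the article plans to test it unadjusted. The bias relative to the true change in extubation time is d days; the observed change is d − e, in either direction. In the illustrations it ranges from 1.5 days longer to 1 day shorter. These sizes rest on assumed timings; the algebra does not. It applies to patients who switch to support after randomisation. For those already in support mode, d is zero if their clock starts at randomisation.

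The control-to-support start is a separate point of wording that needs clarifying. A reader should not infer that the main efficacy conclusion is at risk: the primary outcome runs from the start of ventilation, and the secondary time from randomisation to successful extubation is also free of this problem.

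**What to change.** 1. Redefine control-to-support time as time from randomisation to first support mode, among patients in control mode at randomisation. Mode at randomisation is a baseline characteristic, so this restriction keeps the comparison randomised. Counting the first support mode settles repeat episodes, and the restriction settles patients already in support mode.
2. Use the already listed time from randomisation to successful extubation for the between-arm comparison of weaning.
3. Report support-to-extubation time by arm descriptively, without a between-arm test, and give the number of patients who contribute.

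**Cost.** No new data are needed, since the device records in both arms. One secondary comparison becomes descriptive and another is redefined. That is a change to the planned analysis, so it should be dated and documented before results by arm are seen. The sample size and primary outcome do not change.
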